### Monitoring

A Data Monitoring Committee (DMC) will be established, which is independent of the study organizers. Furthermore, the steering committee, led by the principal investigator, will follow the principles of good clinical practice, including the quality control of the clinical protocol and data management and the organization of team meetings. An annual report will be supplied, in strict confidence, to the DMC about the trial development.

A pilot study will be conducted to assess the feasibility of the protocol, interventions and instruments. Any major modification to the protocol which may impact on the conduct of the study, potential benefit of the patient or may affect patient safety, including significant changes of study design, patient population, sample sizes or study procedures will require a formal amendment to the protocol. Such amendment will be approved by the Bioethics Committee prior to the implementation.

In addition, an interim-analysis will be performed after the pilot study and on the primary end point when 50 % of patients have been randomized and have completed the follow-ups. The interim-analysis is performed by an independent statistician. The statistician will report to the independent DMC, who will have unblended access to all data and will discuss the results of the interim-analysis with the steering committee in a joint meeting. The steering committee decides on the continuation of the trial and will report to the Bioethics Committee.

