Moreover, the most effective interventions to reduce depressive symptoms and prevent depression are multicomponent cognitive-behavioral programs [8, 16]. Specifically, in an indicated prevention intervention, Vázquez and colleagues [11] applied cognitive techniques to change thought patterns (e.g., double-standard technique, priming) and behavioral techniques to active behaviors (e.g., pleasant activities planning, reinforcement). They found a significant reduction in the incidence of depression (1.1 % vs. 12.2 %) and depressive symptoms (Cohen's *d* = 1.05) when compared to the control group. Using a dismantling strategy could help identify the contribution of behavioral activation techniques to the therapeutic change. As a result, this can contribute to the improvement of the prevention program and to greater efficiency. The behavioral activation techniques should play an essential role because assuming the caregiver role entails a number of behavioral changes related to leisure and recreation, family life and work that may involve a loss of positive reinforcement and an increase in aversive experiences, factors relevant to the development of depression [17]. In fact, a link between the shortage of leisure activities for caregivers and depressive symptoms has been previously demonstrated [18]. Furthermore, previous research [19–22] comparing antidepressant medication, cognitive techniques aimed at the automatic thoughts and underlying schemes, and behavioral activation techniques have shown that behavioral interventions are sufficient to effectively and efficiently treat depression.

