### Sample size

Based on previous studies of indicated prevention of depression in caregivers [10, 11, unpublished paper of Note 1] and studies that have administered therapies for depression by phone (see [13]), we estimate that a sample size of 56 participants per group (168 in total) will be sufficient to detect a difference of 19 % in the rates of incidence of depression episodes between experimental and control conditions, assuming α = .05 and a power (1 - β) of .80. However, assuming an attrition rate of 5-8 %, we estimate that the sample size for each of the groups should be approximately 60 subjects (180 in total).

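### The half-way interim results on the primary endpoint are discussed with the investigator-led committee that decides on continuation, which defeats the independent DMC's firewall

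*Protocol article*

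**What the plan says.** The Monitoring section of the protocol article sets up an independent DMC and has an independent statistician run an interim analysis "on the primary end point when 50 % of patients have been randomized and have completed the follow-ups". The statistician reports to the DMC, which has unblinded access to all data (the article prints unblended, which I read as a slip for unblinded).

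The same paragraph then has the DMC meet the trial's leadership: it "will discuss the results of the interim-analysis with the steering committee in a joint meeting". The body in question is "the steering committee, led by the principal investigator", and it also holds the decision: "The steering committee decides on the continuation of the trial".

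The Sample size section gives one error rate, "assuming α = .05 and a power (1 - β) of .80", and does not mention the interim look. Neither does the Statistical analyses section. The article does not say whether the look is for efficacy, futility or safety, and it names no boundary.

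**The concern.** An independent statistician and DMC are used so that those who conduct the trial stay unaware of accumulating comparative results. Here the arrangement is built and then undone by a stated rule: what is discussed is the results, not only a recommendation.

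Several features give such knowledge a route into the data:

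- The primary outcome is a semi-structured diagnostic interview with a stated kappa of 0.61 (Primary outcome measure), so it rests on judgement.
- Dropouts are counted as depressive episodes (Statistical analyses). Retention effort that differed by arm would therefore change the primary result directly, and retention is in the study team's hands (Design).
- The steering committee is responsible for quality control of the protocol and of data management and for team meetings (Monitoring). Therapists are monitored weekly (Interventions), and a study investigator trains the evaluators (Outcomes).

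A second, conditional matter is the error rate. If the look may lead to an early claim of efficacy, the unadjusted use of .05 at both looks would raise the type I error.

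**Working it through.** **1. The roles side by side (all from Monitoring).**

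- Runs the analysis: independent statistician.
- Has unblinded access: DMC.
- Hears the results: steering committee, in a joint meeting.
- Heads that committee: principal investigator.
- Decides on continuation: steering committee.

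The third line removes the separation that the first two create.

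**2. Who is still exposed.** Half of the planned 180 is 90, about 30 per arm, so about 90 participants lie outside the interim set. No accrual rate is given. These 90 may be anywhere between not yet recruited and close to their last visit, so the size of the exposure cannot be fixed. With about 60 per arm, each dropout counted as an episode moves that arm's incidence by 1/60 = 1.7 percentage points, as much as one diagnosed episode. The design difference is 19 points.

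**3. The plan's own sample size.** The article says "a sample size of 56 participants per group (168 in total) will be sufficient to detect a difference of 19" percent, but the two rates are not given. Assuming 25% vs 6%, two-sided .05, power .80, pooled formula without continuity correction:

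- n = [1.960·√(2·0.155·0.845) + 0.842·√(0.25·0.75 + 0.06·0.94)]² / 0.19²
- = (1.003 + 0.416)² / 0.0361 ≈ 55.8, so 56 per group.

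The figure is thus attainable. With lower rates from 0% to 12.2% and the same 19-point difference, n runs from 37 to 73. For attrition, 56/0.95 gives 59 and 56/0.92 gives 61, in line with the stated 60 or so.

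**4. Type I error under different interim rules.** Assumptions: one active-vs-control contrast, two-sided tests, information fraction 0.5, so the two test statistics have correlation √0.5 = 0.707 under the null. Overall error = 1 − P(|Z1| ≤ c1 and |Z2| ≤ c2).

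- c1 = c2 = 1.960 (.05 at both looks, early claim allowed): 0.0831.
- c1 = 3.2905 (p<.001), c2 = 1.960: 0.0502.
- c1 = 3.2905, solved for an overall .05: c2 = 1.962, final p threshold 0.0498.
- O'Brien-Fleming: c1 = 2.797, c2 = 1.977, nominal p 0.0052 then 0.0480.
- Futility or safety only, no early efficacy claim: not above .05.

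**5. Does the sample size show that no boundary exists?** The O'Brien-Fleming inflation factor is 1.0078, and 56 × 1.0078 = 56.4, so 57 per group. At an unchanged 56 the power is 0.797. A change of one per group disappears in the rounding to about 60, so the sample size cannot tell whether a boundary was planned.

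**The case against.** The best defence has three parts.

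*The article is silent on alpha, not wrong.* A reader might infer that this is an efficacy look that spends no alpha and that type I error therefore exceeds 5%. The text does not support that. It states no purpose, test or threshold, and boundaries are commonly left to an analysis plan, charter or full protocol that is not shown. The single .05 is compatible with an adjusted design, as step 5 shows. This part of the objection stands. It would also be wrong to add the multiplicity of the two active-vs-control contrasts to the interim problem: that is a separate matter.

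*Disclosure by arm is not stated.* Unblinded access is given to the DMC, and the results discussed might be coded or pooled, which would do much less harm. This stands as a limit on what can be asserted. It does not remove the point, because nothing in the text restricts what is discussed.

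*Bias has few routes.* Evaluators are meant to be unaware of the purpose, the interventions and the allocation, and if recruitment were fast, treatment of the remaining half could largely be over. A reader might go further and infer that most participants will already be enrolled by the time of the look. Without an accrual rate, neither that nor its opposite can be claimed. Blinded evaluators do reduce the risk in the interview itself, but retention, oversight and the continuation decision stay with people who have heard the results.

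A steering committee that takes the final decision is not a defect in itself. The defect is that it decides after discussing the results.

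**Conclusion.** The governance point holds on the plan's explicit wording. Followed as written, the plan lets the trial's leadership learn interim results on the primary endpoint before the remaining follow-up is complete. An analysis plan or charter could not cure this without contradicting the article. The resulting bias cannot be quantified from the document, since neither the accrual rate nor the level of detail disclosed is given. Once the joint meeting has taken place, the disclosure cannot be reversed, so the text needs changing before the look.

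The error-rate point holds only conditionally. It is about 8.3% per contrast if efficacy can be claimed at two-sided .05 at both looks, about 5.0% with an interim threshold of p<.001, and not inflated if no early efficacy claim is possible. These figures assume equal information in the two halves and two-sided testing, which the article does not state.

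**What to change.** In Monitoring, replace the joint discussion of results with a rule that the DMC gives the steering committee only a recommendation (continue, modify or stop). Comparative results stay with the DMC and the independent statistician until the final analysis. The steering committee can keep the decision on continuation, taken on that recommendation.

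In the same place, state the purpose of the look, in one of two ways:

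- no early claim of efficacy is allowed, and the final test stays at .05; or
- efficacy stopping is allowed only under a strict boundary, for example Haybittle-Peto with p<.001 at the interim and about .0498 at the final test.

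The cost is a few sentences and a line in the DMC charter, with a formal amendment if the article's own rule on major modifications is judged to apply. The strict boundary leaves the final threshold almost unchanged. The small downside is that early stopping for efficacy becomes unlikely.

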### Ethical issues

All human rights and the dignity of the subjects of the study will be protected according to the Declaration of Helsinki. All procedures in the study have been approved by the Bioethics Committee of the University of Santiago de Compostela (Spain). All participants will be guaranteed confidentiality and will need to give informed consent (first verbally by phone and then in written form using a form that will be mailed to them). Participation in this study will be completely voluntary and participants will not receive any kind of incentive, financial or otherwise.

During the course of the study, if a caregiver develops a major depressive episode, they will be removed from the study and referred to mental health services available in the community for treatment.

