### Participants, recruitment and eligibility criteria

Participants will be recruited from the Official Register of Caregivers of the Ministry of Labor and Welfare of the Galicia Regional Government in northwestern Spain. A random sample of caregivers stratified by area type [rural (<2000 inhabitants) or urban (≥2000 inhabitants)] and province (Coruña, Lugo, Pontevedra or Orense) will be selected. Previously we have determined that approximately 39 % and 44 % of caregivers have elevated depressive symptoms [10, 11] and 8.9 % have depressive episodes [5]. As a result, to achieve the estimated sample size of approximately 180 participants we will need to randomly select approximately 550 caregivers for a screening prior to the verification of the eligibility criteria.

Caregivers will be contacted by mail and invited to participate in the study. They will be asked to return a stamped postcard if they do not want to be contacted further. Caregivers who do not return that card will be contacted with a brief description of the study. Those who are interested will undergo a screening to assess depressive symptoms and history of depressive episodes. Those who meet the initial selection criteria will be invited to participate in a longer evaluation that will evaluate the inclusion and exclusion criteria.

To be enrolled in the study, participants must meet the following inclusion criteria: (a) be officially recognized by the authorities as caregivers for a relative in a situation of dependency, (b) have a telephone, (c) obtain a pretreatment score ≥ 16 in the Center for Epidemiologic Studies Depression Scale (CES-D [25]), (d) not meet the DSM-IV criteria for a major depressive episode [26], (e) not have a history of major depression, (f) give informed consent. We will exclude those subjects that at the time of the assessment: (a) have been receiving psychological or pharmacological treatment for the last two months, (b) experience other conditions that could act as confounders in the study (e.g., symptoms due to the direct physiological effects of a substance or a medical condition), (c) have medical and mental disorders of such severity that they require immediate intervention (e.g., suicidal ideation) or that would make it impossible to participate in the study (e.g., severe hearing impairment), (d) care for a family member that has a terminal diagnosis, (e) are planning to institutionalize the family member or to move.

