### Statistical analyses

All analyzes will be conducted in accordance with the principle of intention to treat. All participants will be analyzed in the group to which they were assigned. The most conservative approach for attrition will be adopted by considering dropouts as a treatment failure (i.e., a major depressive episode was triggered) and by replacing missing data with the corresponding baseline scores. Cumulative incidence rates of depression for all three groups will be calculated to examine the efficacy of the interventions on prevention of major depressive episodes. The relative risk (RR) and number needed to treat (NNT) will be calculated according to the formulas proposed by Guyatt et al. [38]. Also, the time it takes for the participants to suffer a major depressive episode will be analyzed using a survival analysis. The effect of the interventions on depressive symptoms will be examined by using mixed factorial analysis of variance (ANOVA) tests with repeated measures. To examine the relationship of the received interventions and depressive symptoms as mediated by change in automatic negative thoughts, self-efficacy, and reinforcement, we will utilize the method recommended by Baron and Kenny [39]. The acceptability and adherence to interventions will be examined by using the Chi-Square test to compare the percentages of dropouts and the Student *t*-test for independent samples will be used to compare session attendance and homework completion. The level of participant satisfaction with the interventions will be analyzed with frequency distribution of each item in the CSQ-8, and we will compare results across both conditions using the Student *t*-test for independent samples. All analyzes will be conducted using SPSS for Windows, version 20.0.

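### Removing participants at a depressive episode and filling their later CES-D with baseline scores analyses them as unchanged in symptoms, with a bias of no assured direction

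*Protocol article*

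**What the plan says.** All references are to the protocol article.

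- **Ethical issues:** "if a caregiver develops a major depressive episode, they will be removed from the study and referred to mental health services". The removal is from the study, not only from the intervention.
- **Outcomes, Table 1:** major depression by SCID-CV is primary. CES-D is secondary, with assessments before and after treatment and at 1, 3, 6 and 12 months.
- **Participants, recruitment and eligibility criteria:** caregivers must "obtain a pretreatment score ≥ 16 in the Center for Epidemiologic Studies Depression Scale" and must "not meet the DSM-IV criteria for a major depressive episode". The baseline score is thus elevated but precedes any episode.
- **Statistical analyses:** attrition is handled by "considering dropouts as a treatment failure (i.e., a major depressive episode was triggered") and "by replacing missing data with the corresponding baseline scores". The section presents this as the most conservative choice and makes no exception for participants removed at an episode. It adds: "The effect of the interventions on depressive symptoms will be examined by using mixed factorial analysis of variance (ANOVA) tests with repeated measures".
- **Background (objectives):** the central hypothesis covers both episodes and symptoms, after treatment and at every follow-up.

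**The concern.** The two rules are each stated plainly, but they do not work together. Removal at the event stops CES-D collection in the participants whose symptoms have just crossed the diagnostic threshold. The imputation rule then gives them a score from a time when, by the entry criteria, they had no episode. Their change from baseline is set to zero at each later visit.

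The same sentence on attrition also treats one person in two ways: a dropout has had an episode for the incidence analysis, but is unchanged from a non-episode baseline for CES-D.

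At stake is the symptom comparison, which is secondary in Table 1 but is half of the central hypothesis. Scores that are never collected cannot be recovered at the analysis stage. Single imputation also enters the substituted values as if they had been observed.

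**Working it through.** **Inputs from the article.** Design difference in episode incidence 19 percentage points; 56 per group, about 60 after attrition of 5-8 % (Sample size). Incidence of 12.2 % against 1.1 % in an earlier face-to-face prevention trial (Background). CES-D range 0 to 60, higher is worse (Secondary outcome measures).

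**Assumptions, not in the article.** The two arm rates behind the 19 points; the true mean change from baseline, w, after an episode (taken as equal in both arms); the changes and SD among other participants.

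**The plan's own figure.** A two-sided test of 25 % against 6 % without continuity correction gives 56 per group (power 0.802). 56/0.95 = 59 and 56/0.92 = 61, in line with about 60. Other pairs of rates and test variants also come close to 56, so 25 % and 6 % serve only as an illustration.

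**Step 1: how many are affected.** By the last visit, 60 × 0.25 = 15 controls and 60 × 0.06 = 3.6 per intervention arm would have had an episode. This is an upper limit for substituted scores. An episode found at 12 months leaves no later visit, and the article does not say whether CES-D is still taken at the visit where the episode is diagnosed.

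**Step 2: effect on the mean contrast.** Substitution replaces w by 0 in a share p of each arm, so each arm's mean change is understated by p × w. The control-minus-intervention contrast loses (p_c − p_t) × w.

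- Design difference: 0.19 × 5, 10, 15 = 0.95, 1.9, 2.85 points.
- Earlier trial's rates: (0.122 − 0.011) × 5, 10, 15 = 0.56, 1.11, 1.67 points.
- If removed caregivers improve on referral, w is negative and the sign reverses: 0.19 × (−5) = −0.95, so the benefit is overstated by 0.95.

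**Step 3: effect on spread, at one visit.** Assume that the others change by −2 (control) and −8 (intervention), with SD 8 within each subgroup. Write m for the others' mean change.

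- Variance with true scores: 64 + p(1−p)(w − m)².
- Variance after substitution: 64(1−p) + p(1−p)m².
- Contrast after substitution: 0.75 × (−2) − 0.94 × (−8) = 6.02, whatever w is. The true contrast is 6.02 + 0.19w.
- Standardised contrast: contrast divided by the root of the mean of the two arm variances.

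| w | True contrast | Analysed contrast | True control SD | Analysed control SD | True standardised | Analysed standardised |
|---|---|---|---|---|---|---|
| −5 | 5.07 | 6.02 | 8.1 | 7.0 | 0.63 | 0.80 |
| 0 | 6.02 | 6.02 | 8.0 | 7.0 | 0.74 | 0.80 |
| 5 | 6.97 | 6.02 | 8.6 | 7.0 | 0.81 | 0.80 |
| 10 | 7.92 | 6.02 | 9.5 | 7.0 | 0.85 | 0.80 |
| 15 | 8.87 | 6.02 | 10.9 | 7.0 | 0.86 | 0.80 |

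The analysed result is the same in every row, so it carries no information on what happened to symptoms after an episode. The control SD is reduced in all of them. Even with no bias in the mean (w = 0), the standardised contrast is inflated, from 0.74 to 0.80.

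**Step 4: ordinary dropouts.** Let fall be the drop in CES-D that dropouts would have shown. Substitution moves the contrast by p_c × fall_c − p_t × fall_t, where positive favours the intervention. At the ends of the planned attrition (8 % control, 5 % intervention):

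- falls of 2 and 8: 0.08 × 2 − 0.05 × 8 = −0.24, against the intervention;
- falls of 2 in both arms: 0.08 × 2 − 0.05 × 2 = +0.06, in its favour.

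This component is small at the planned attrition and can take either sign.

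**The case against.** The strongest defence has four parts.

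1. *The primary analysis stands.* The episode is recorded before removal, so cumulative incidence, relative risk, NNT and time to episode are not changed by this mechanism. This is correct. A reader who inferred that the main result is compromised would go beyond the text.

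2. *Intention to treat is kept.* A reader might infer that the rule breaks the statement "All analyzes will be conducted in accordance with the principle of intention to treat". It does not: the section goes on to say that everyone is analysed in the assigned group, and substitution keeps them there. What is lost is outcome follow-up, not assignment.

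3. *The bias is conservative and overstated.* Where removed caregivers stay worse than baseline and are more numerous among controls, the mean contrast is indeed diluted. The 0.95 to 2.85 points are also upper-end figures: they need every event to precede the visit and the worsening to persist despite referral. Both points stand as limits on size. They do not establish that the rule is conservative, because the sign depends on the course after referral, which the plan would not observe.

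4. *The model is a matter for the analysis plan.* A reader might also infer that "mixed factorial analysis of variance (ANOVA) tests with repeated measures" is wrong in itself, for instance because baseline may enter as one of the repeated measures. The article does not state which term or contrast carries the inference, and a condensed article may leave that out. This is a separate question of efficiency and no part of the point.

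**Conclusion.** The point holds for CES-D. Read together, the Ethical issues and Statistical analyses sections replace post-episode symptom scores with pre-episode ones, and this follows from the text without assumptions. Its size does rest on assumptions: up to 0.95 to 2.85 points of dilution at the 19-point design difference for a true mean worsening of 5 to 15 points, if all events precede the visit; less at the earlier trial's rates; and overstatement if removed caregivers fall below baseline. Ordinary dropouts add a small term of either sign. The net direction cannot be fixed in advance, so the claim of a most conservative approach is not supported.

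A reader might take the reduced SD as proof that the trial's standard errors will be too small. The calculation illustrates that risk at a single visit under assumed values. It does not measure it for the planned six-visit analysis.

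**What to change.** 1. **Reconcile the two sections.** State that referral, which is not in question here, does not end outcome collection. Continue the scheduled mailed CES-D and telephone SCID after an episode for participants who agree. Whether such a participant stays in the intervention is a clinical matter for the investigators to state clearly.
2. **Analyse observed scores.** Use a likelihood-based mixed model for repeated measures on all observed post-baseline CES-D, with group, visit, group-by-visit and baseline CES-D.
3. **Demote the substitution rule.** Keep baseline carried forward as a sensitivity analysis only, and drop the description of it as most conservative for CES-D.

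The first change matters most. A mixed model alone does not restore scores that the removal rule prevents from being collected.

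Cost: an amendment to the wording and a few extra assessments of people who have had an episode, on a schedule and by routes (post and telephone) already in place. The sample size and the primary analyses need no change on this account.
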